## Abstract

**Background & Objectives::**

Hypoferritinemia without anemia (HWA) is an under-recognized public health concern. Early identification and targeted treatment of HWA can prevent unnecessary medication use and potential drug abuse. This study aims to establish clearer guidelines for recognizing and managing HWA, improving patient’s outcome. The study objectives will be to compare the treatment efficacy of oral and IV iron on patients with HWA and to check the severity of clinical indicators of HWA post treatment among reproductive age women.

**Methods::**

We will choose a multicenter, multi-arm randomized controlled trial with a parallel assignment interventional model. About three hundred participants (n=300) aged 18-45 with hypoferritinemia without anemia and no comorbidities will be recruited. Participants will be randomized into three groups of one hundred each: Group-A will receive oral iron supplements (Iron III Hydroxide Polymaltose Complex, 100 mg elemental iron) one tablet per day for three months; Group-B will receive intravenous iron (Ferric carboxymaltose, one dose per month for three months); Group-C will receive no treatment. All groups will be followed for four months.

**Conclusion::**

The primary outcome will be the change in serum ferritin levels among groups at four months post-intervention. Secondary outcomes will include changes in clinical symptoms post-intervention. Data will be analyzed by using independent t-tests for between-group ferritin levels, paired t-tests for within-group comparisons, Wilcoxon Rank and Friedman tests for clinical symptoms, and ANOVA for comparisons across multiple groups.

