### Outcome Measures:

### Primary Outcome:

The primary outcome will be change in serum ferritin levels from baseline to Visit five. This will be measured by analyzing the difference in the treatment outcome of oral iron supplementation Group-A, intravenous iron supplementation Group-B and no treatment Group-C, four months post-intervention. A 5ml blood sample for measuring serum ferritin levels will be drawn by the phlebotomist at visit five to access the change in the value of serum ferritin from baseline.

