### Statistical Analysis:

SPSS version 24 will be used for data analysis. Descriptive and inferential statistics will be used. Comparisons will be made using independent sample t-tests, paired sample t-tests, Wilcoxon rank tests, Friedman tests, and ANOVA, as appropriate based on normality assessed by the Shapiro-Wilk test.

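### The primary outcome is change in ferritin, but the between-group tests named are unadjusted and leave the measured baseline unused

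*Protocol article*

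**What the plan says.** - **Outcome.** Under Outcome Measures, Primary Outcome: "The primary outcome will be change in serum ferritin levels from baseline to Visit five". The Visit 5 sample is drawn "to access the change in the value of serum ferritin from baseline". The abstract's Conclusion paragraph agrees: "The primary outcome will be the change in serum ferritin levels among groups at four months post-intervention".
- **Tests, abstract.** The same paragraph assigns "independent t-tests for between-group ferritin levels", "paired t-tests for within-group comparisons" and "ANOVA for comparisons across multiple groups". It ties the Wilcoxon and Friedman tests to clinical symptoms.
- **Tests, Statistical Analysis section.** "Comparisons will be made using independent sample t-tests, paired sample t-tests, Wilcoxon rank tests, Friedman tests, and ANOVA", chosen "as appropriate based on normality assessed by the Shapiro-Wilk test". No other condition for choosing a test is given.
- **Baseline.** The trial steps in Methods place a serum ferritin sample at Visit 0, before randomisation. Ferritin below 30 ng/ml is an inclusion criterion, so every randomised woman has a baseline value.
- **What is not named.** The article names no between-group test of change, no model that uses baseline and no unequal-variance method. It gives no ferritin SD at any time point.

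**The concern.** The outcome and the between-group test do not match: one is a change, the other a comparison of levels. The only listed tests that measure change from baseline are the paired ones, and these are uncontrolled. Women enter because a screening ferritin was low, so some rise is possible in every arm, including the untreated one, through regression to the mean. A paired test cannot separate that from a treatment effect.

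The between-group tests are controlled but ignore a covariate that has already been collected. That costs precision.

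There is a second, smaller issue. Classical ANOVA uses one error variance for all three arms. All women start below 30 ng/ml; one arm then receives repeated intravenous iron and another receives nothing. It is reasonable to expect different spreads at Visit 5, and neither the ANOVA nor the normality check allows for that.

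**Working it through.** **The plan's own figure.** The only figure that can be reproduced is the 96 per group in Sample Size. With p1 = 0.417, p2 = 0.417 × 0.55 = 0.229, two-sided 5% and 80% power (alpha and power are assumed; neither is stated), the pooled two-proportion formula gives 97. This is close to the plan, but it concerns proportions. It supplies no ferritin SD or correlation and does not bear on this point, so the rest uses assumed ranges.

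**1. Gain from baseline adjustment.** With r the within-arm correlation between baseline and Visit 5 ferritin, variance under ANCOVA ÷ variance of the unadjusted comparison of levels = 1 − r².

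| r (assumed) | 1 − r² | Variance removed | n per arm matching an unadjusted 100 |
|---|---|---|---|
| 0.1 | 0.99 | 1% | 99 |
| 0.3 | 0.91 | 9% | 91 |
| 0.5 | 0.75 | 25% | 75 |
| 0.6 | 0.64 | 36% | 64 |

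The entry cap of 30 ng/ml narrows the baseline range, and two arms are treated. Both weaken the correlation, so 0.1–0.3 is the more plausible part of the range.

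**2. If the t-test were run on change scores.** Variance of change ÷ variance of levels = (s_b² + s_p² − 2·r·s_b·s_p) / s_p². With assumed baseline SD s_b = 7 and Visit 5 SD s_p = 10:
- r = 0.1: (49 + 100 − 14)/100 = 1.35
- r = 0.3: (49 + 100 − 42)/100 = 1.07
- r = 0.5: (49 + 100 − 70)/100 = 0.79

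The ANCOVA values are 0.99, 0.91 and 0.75. ANCOVA has the smaller variance in each case, and at low r the change score is worse than the unadjusted level.

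**3. Unequal spread and the pairwise t-test.** With n in each arm, the pooled two-sample standard error is √[((s_A² + s_C²)/2)·(2/n)] = √[(s_A² + s_C²)/n], which is the Welch standard error. The third arm does not enter. In simulation (20,000 normal runs, 100 per arm, SDs for A/B/C from 15/30/10 to 20/100/10 ng/ml, all assumed) the t-test's level was 4.7–5.5%.

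**4. Unequal spread and ANOVA.** Under the same settings the F test's level was about 6.5–8%.

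**5. Contrasts on the ANOVA error term, if anyone used them.** Pooled standard error = √[(s_A² + s_B² + s_C²)/3]·√(2/100).

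| SD A/B/C | Pooled SE | True SE, A−C | Ratio | True SE, B−C | Ratio |
|---|---|---|---|---|---|
| 15/30/10 | 2.86 | 1.80 | 1.59 | 3.16 | 0.90 |
| 15/60/10 | 5.12 | 1.80 | 2.84 | 6.08 | 0.84 |
| 20/100/10 | 8.37 | 2.24 | 3.74 | 10.05 | 0.83 |

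The A−C contrast would be far too cautious: a true difference that the t-test detects with about 80% power is detected with 38% in the first row and under 1% in the other two. The B−C contrast would be too liberal, with a level of 7.6–10.1%.

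**6. Unequal arms.** Step-3 of the Recruitment Strategy describes simple randomisation. If arm sizes are left to chance, each has SD √(300 × 1/3 × 2/3) = 8.2. At 112/88/100 (12/8.2, about 1.5 SD off in two arms), the B−C t-test runs at 6.3–6.7% and F at 8.0–10.9%.

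**The case against.** **The damaged procedure is not in the plan.** A reader might infer from step 5 that the A−C comparison will have a standard error several times too large and almost no power, and that comparisons with the intravenous arm will have a false-positive rate near 10%. The article does not support that. Those results need pairwise contrasts built on the three-arm ANOVA error, and no section names such contrasts. The pairwise method it names is the two-sample t-test, which uses only its own two arms. This objection stands: step 5 is a warning about a possible follow-up to the ANOVA, not a finding about the plan as written.

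**The comparison is valid.** A reader might also infer that ignoring baseline biases the result. It does not; in a randomised trial the unadjusted comparison of levels is unbiased. This stands too.

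**The sizes are assumed.** No SD or correlation is documented, and at r of 0.1–0.3 the gain is worth only 1 to 9 women per 100. This stands, and the ranges above should be read accordingly.

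**Levels may be shorthand for change.** This is possible in a one-line abstract list, and the Statistical Analysis section does not say what quantity is tested. But that section does not correct the abstract either, and step 2 shows that a t-test on change would still be less efficient than adjustment.

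**Details belong in an analysis plan.** An unseen plan may settle covariates and scale. But the article does more than stay silent: it names the tests, and the named between-group test does not fit the named outcome. The Shapiro-Wilk condition does not repair this, since it concerns neither baseline nor variance.

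**Conclusion.** The point holds as a mismatch between outcome and test, and as an avoidable loss of precision. It is not a threat to validity.

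- **Certain from the text:** the outcome is change; the named between-group ferritin test is on levels, with no covariate; baseline is used only in uncontrolled within-arm tests.
- **Size of the precision loss:** 1% of variance at r = 0.1, 9% at 0.3, 25% at 0.5 and 36% at 0.6, with the low end more plausible. All values of r are assumptions.
- **Unequal spread:** plausible from the regimens but undocumented. Under the assumed SDs the F test is mildly anti-conservative, about 6.5–8% with equal arms. Pairwise t-tests with near-equal arms are not materially affected. Contrasts taken from the ANOVA error term would be miscalibrated, but the article does not plan any.

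The change is worth making because it is nearly free and settles the outcome, the baseline and the variance question in one sentence.

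**What to change.** Name one primary between-group analysis in the Statistical Analysis section and bring the abstract into line with it:

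- ANCOVA of Visit 5 ferritin, preferably log-transformed, on arm and baseline ferritin on the same scale. With baseline as a covariate, modelling the level or the change gives the same arm effect, so the mismatch disappears.
- Robust or unequal-variance standard errors, so that no arm's spread is imposed on another.
- The B−A, A−C and B−C contrasts, each with a 95% confidence interval.
- The within-arm paired tests kept as descriptive only.

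**Cost:** wording only; the baseline sample is already scheduled. On the log scale effects become ratios of geometric means instead of ng/ml differences; back-transformed means can be reported beside them.

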
### Research Objectives:

To compare the effects of` oral iron (Iron III Hydroxide Polymaltose Complex eq. to Elemental Iron, 100 mg per day for three months) supplementation (Group-A) versus Intravenous (IV) iron (Ferric carboxymaltose 500 mg, three doses for three months) (Group-B) versus no treatment (Group-C) on serum ferritin level, four months post-intervention.To evaluate the change in the severity of clinical indicators of Hypoferritinemia without Anemia between Group A, B and C, four months post-intervention.

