## METHODS

### Study Design:

This single-blinded, multicenter, multi-arm, randomized controlled trial (RCT) will employ a parallel assignment interventional model.

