### Recruitment Strategy

### Participants will be recruited in three steps:

***Step-1:*** Purposive sampling of individuals who provide informed consent and meet the serum ferritin and hemoglobin criteria.

***Step-2:*** Screening based on inclusion and exclusion criteria, including blood tests for thyroid function and blood sugar.

***Step-3*:** Random assignment to groups A, B, or C via simple random sampling using a computer-generated list.

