### The trial will follow seven steps guided by the CONSORT guidelines:

***Recruitment of participants (Visit 0, Week 1):*** Study participants will be selected after signing the informed consent and meeting the eligibility criteria of the study. Blood sample for CBC and serum ferritin will be taken by the phlebotomist.

***Baseline data (Visit 0, Week 1):*** Baseline data will be recorded for eligible participants. The baseline data will include the socio-demographics information of the study participants and history of clinical symptoms of iron deficiency (pre intervention).

***Assessment of Eligibility (Visit 1, Week 1):*** Participants will be screened based on the results of CBC and serum ferritin. Blood samples of eligible participants will be collected for blood sugar and thyroid functions.

***Randomization (Visit 2, Week 2):*** Eligible participants with normal range of thyroid and blood sugar levels will be randomized to any of the three groups by using simple random sampling.

***Allocation (Visit 2, Week 2):*** After randomization, participants will be assigned to Groups A, B, or C, with specific intervention outlined.

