### Intervention:

***Visit 2 (Week 2):*** First dose of oral or IV iron will be administered, and adverse effects will be monitored.

***Visit 3 (Week 6):*** Second doses will be administered; compliance and adverse effects will be monitored.

***Visit 4 (Week 10):*** Third doses will be administered; compliance and adverse effects will again be monitored.

***Post-Intervention Data Collection (Visit 5, Week 16):*** The participants from all three study groups will be contacted. Blood samples have to be collected to measure the efficacy of iron treatment on ferritin levels. The symptoms severity levels will also be recorded again to assess the effectiveness of the intervention.

***Compliance:*** To enhance compliance, participants in Group-B will receive daily reminder messages or calls regarding their supplementation regimen.

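### The Friedman test named for clinical symptoms fits neither the three independent arms nor the two symptom assessments, and no three-group rank test is named in its place

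*Protocol article*

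**What the plan says.** The Study Design section describes a "multi-arm, randomized controlled trial (RCT) will employ a parallel assignment interventional model". The abstract's Methods give three groups of 100, and Recruitment Strategy specifies "Random assignment to groups A, B, or C via simple random sampling using a computer-generated list". No matching, triplets or blocks tie a woman in one arm to a woman in another.

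The second research objective is "To evaluate the change in the severity of clinical indicators of Hypoferritinemia without Anemia between Group A, B and C", so the question is a comparison between arms. Symptom history is taken at Visit 0 as part of the baseline data. Of Visit 5 (week 16) the Intervention section says "The symptoms severity levels will also be recorded again to assess the effectiveness of the intervention". Table-I agrees: baseline data at Visit 0, post-intervention data at Visit 5, and at Visits 2 to 4 only randomisation, medication and adverse event monitoring.

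For the analysis, the abstract's Conclusion gives t-tests for ferritin and then "Wilcoxon Rank and Friedman tests for clinical symptoms, and ANOVA for comparisons across multiple groups". The Statistical Analysis section lists the t-tests followed by "Wilcoxon rank tests, Friedman tests, and ANOVA, as appropriate based on normality assessed by the Shapiro-Wilk test". No rank or ordinal method for three or more independent groups is named anywhere in the article.

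**The concern.** Friedman is a test for related samples: the same subjects, or matched blocks, seen under at least three conditions. The trial offers three conditions (the arms) on unrelated women, or related measurements on only two occasions. Neither arrangement meets the requirement.

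What is at stake is the second objective. The Sample Size section also frames its hypothesis in terms of symptom scores under IV iron against oral or no treatment, so this comparison is not peripheral. If the wording stands, the analyst must either run a test that does not answer the question or pick another after the data are in.

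**Working it through.** The article gives no severity scale, SD or effect size for symptoms, so there is no planned figure to reproduce. The check sets the design against the test's requirements. The simulations that follow rest on assumed inputs.

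**1. Within women (2 occasions).** Friedman's statistic for n subjects and k conditions is 12/[n k (k+1)] × ΣR² − 3n(k+1), where R is the rank sum of a condition. Put k = 2 and let b of n women improve, with no ties. The rank sums are n + b (Visit 0) and 2n − b (Visit 5). Then

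(2/n) × [(n + b)² + (2n − b)²] − 9n = (2b − n)²/n.

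This is the sign-test chi-square. Arm does not appear in it.

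A numerical example: suppose all 300 women change by 0.3 SD of the within-woman change, with no difference between arms (assumed).
- P(improve) = Φ(0.3) = 0.618.
- Mean of z = (2 × 0.618 − 1) × √300 = 4.08; SD of z = 2√(0.618 × 0.382) = 0.972.
- P(z > 1.96) = Φ[(4.08 − 1.96)/0.972] ≈ 0.986.

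Simulation also gave 98.6%. The test is significant almost every time although the arms do not differ. The no-treatment arm is there to separate such a common change from a treatment effect.

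**2. Across arms (3 conditions).** Each row would hold one woman from each arm, joined only by file position. Rows must be complete and arms equal in size. If allocation is unrestricted, the chance of exactly 100/100/100 is about 3^1.5/(2π × 300) = 5.196/1885 ≈ 0.3%. If the computer list forces equal arms, loss to follow-up (5% is allowed for) can still make them unequal.

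Simulation inputs, all assumed: 95 women per arm, a four-level score cut at −1, 0 and 1 on a latent normal scale, arms shifted by 0, −s/2 and −s, and α = 0.05. There were 1,500 trials per setting for the first three rows and 2,500 in a separate run for the last two.

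| | s = 0.35 | s = 0.45 | s = 0.50 |
|---|---|---|---|
| Kruskal-Wallis power | 0.52 | 0.73 | 0.81 |
| Friedman power, arbitrary rows | 0.47 | 0.68 | 0.75 |
| Friedman verdict changes after reordering rows | 16% | 13% | 12% |
| ANOVA power (second run) | 0.51 | 0.74 | 0.83 |
| Kruskal-Wallis power (second run) | 0.51 | 0.73 | 0.82 |

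In the second run type I error was 0.055 for Friedman and 0.050 for ANOVA. The harm across arms is therefore arbitrariness and some lost power, not false positives.

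**3. What the normality rule leaves.** In simulation a four-level score, or its change, failed Shapiro-Wilk in every run. Under the article's own rule the remaining tests are then Wilcoxon (two samples) and Friedman (related samples). If Wilcoxon means signed-rank, it is a within-arm test. If it means rank-sum, it compares arms in pairs but gives no overall test, and three unadjusted pairs carry a family-wise error of about 1 − 0.95³ = 14% (treating the pairs as independent).

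**The case against.** The strongest reply is that a three-group test is already listed. The abstract names ANOVA for multiple groups without confining it to ferritin, and on the assumed four-level score it matched Kruskal-Wallis in power and held its type I error. This stands. A reader might infer that the trial has no valid multi-group test at all, and the article does not support that. The gap opens only when the Shapiro-Wilk rule turns the analyst away from ANOVA.

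Second, Wilcoxon may mean rank-sum, in which case pairwise comparisons of arms are already provided. That is possible, but the text does not settle it, and it supplies neither an overall test nor a multiplicity adjustment.

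Third, no passage says that women will be paired by row number. True: the row-order figures show what applying Friedman across arms would entail, not a stated intention. The other available use, within women, does not compare arms.

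Fourth, an article may leave model details to a full protocol or analysis plan. It may, but here the article names an unsuitable test in two places, which is different from leaving one unnamed.

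**Conclusion.** The concern holds for clinical symptoms. Friedman is the wrong test for this design, and under the plan's own normality rule it leaves the second objective without a valid three-group rank test. The misfit follows from the design alone. The sizes (12-16% of verdicts changing with row order, 5-6 points of power) rest on an assumed severity scale, shifts and arm size.

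Two further inferences are not supported:
- A reader might infer that ferritin would also end up with Friedman. The abstract assigns t-tests to ferritin and Friedman to symptoms. The article gives no ferritin distribution, and a baseline ceiling of 30 ng/ml does not fix the shape of the change to Visit 5.
- A reader might infer that within-arm use wastes a third of the patients, from the efficiency ratio of sign test to signed-rank test, 0.637/0.955 = 0.67. That ratio is for continuous normal data. On the assumed four-level score the power was about 0.52 against 0.57, and 0.67 against 0.72. The signed-rank test may in any case already be listed.

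This should be fixed before analysis. It concerns the outcome labelled secondary, and no data are lost by correcting it now.

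**What to change.** In both the abstract's Conclusion and the Statistical Analysis section, replace Friedman with a method for independent groups on the symptom outcome. One suitable choice is Kruskal-Wallis on the change in severity from Visit 0 to Visit 5, with multiplicity-adjusted pairwise rank-sum (Mann-Whitney) tests. Ordinal regression of Visit 5 severity on arm and baseline severity is an acceptable alternative. State which Wilcoxon test is meant, and keep the signed-rank test only to describe change within each arm.

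The cost is two sentences of wording. The procedures are available in the planned SPSS version, and no visit, measurement or sample size changes.

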## INTRODUCTION

Iron Deficiency Anemia (IDA) is a widely recognized condition affecting over one billion people globally, however Hypoferritinemia without Anemia (HWA) is estimated to be at least twice as prevalent.^1^ In clinical practice, hypoferritinemia without anemia can be ascertained in adults (ages 15 to 45) when hemoglobin levels are normal (≥12 g/dl) but ferritin levels dip below 30 ng/ml.^1^ According to a study conducted on iron treatment among healthy males and females aged >15 years, a ferritin cut-off of 30 ng/ml is recommended.^2^,^3^ Another study on iron deficiency without anemia shows that the serum ferritin concentration (cut off <30 ng/ml) is the most specific test used for the identification of iron deficiency.^4^ The common symptoms of HWA include fatigue, poor work productivity, cognitive difficulties, hair loss, palpitations, sore tongue, restless leg syndrome, and poor skin, hair, and nail health.^5^,^6^ Despite its prevalence, HWA is frequently overlooked by clinicians, likely due to suboptimal screening practices and reliance on hemoglobin levels alone for diagnosis.^7^ Some patients with HWA may have had profound symptoms for many years while their blood count has been normal throughout.^8^ The normal Complete Blood Count (CBC) results make HWA a hidden disease with a lack in exact underlying cause.^9^ Similar symptoms are experienced by patients suffering from iron deficiency anemia (IDA) and HWA however, the sufferers of the latter condition suffer from wrong or no diagnosis as compared to IDA which is easily diagnosed through complete blood count (CBC).^9^ Because the symptoms and signs of HWA are not specific, which may occur in other physiological or psychiatric conditions, patients with HWA are either suggested no tests or can result in expensive tests for heart or renal failure as a result of complication of chronic iron deficiency,^5^,^10^,^11^ which may be avoidable if simple, cost-effective tests such as serum ferritin, folic acid, and vitamin B12 are conducted on time.^12^,^13^ HWA presents a diagnostic challenge as it mimics the symptoms of IDA, yet remains undiagnosed due to normal hemoglobin and CBC results.^5^ Clinicians generally recommend iron assessments when there has been evidence of anemia, resulting in undetected HWA.^4^ The clinician typically does not make an effort to identify the underlying cause of the symptoms, with the exception of chronic disease study, and instead prescribes symptomatic treatment, which might lead to drug misuse or overmedication e.g., pain killers, anti- depressants or anti-anxiety drugs, sleeping tablets and overdose of multivitamins.^14^-^15^ This study aims to bring attention to the under-recognition of HWA, advocating for better diagnostic protocols and targeted treatments to the clinicians. This study has to be carried out because not only it will help patients determine the category of HWA, but it will also assist them to obtain specific treatment, reducing their risk of drug misuse and overmedication. To date, no study on HWA has been conducted in Pakistan on non-pregnant women, highlighting the need for research in this population.
